**FIGURE 1 F1:**
[figure not shown]
The flowchart of the study protocol.

### Recruitment

Participants will be recruited from patients with APE who met the inclusion criteria in the urology clinic of Chongqing Traditional Chinese Medicine Hospital. Because it is not currently standardized, three senior physicians with a concurrent diagnosis of APE according to the ISSM definition of acquired premature ejaculation (a clinically significant and troubling reduction in ejaculatory latency time, usually about 3 min or less) are required for inclusion in this trial (Salonia et al., 2021). Eligible participants will sign the informed consent form before randomization.

### Participants

#### Inclusion criteria

1. Males whose age were between 18 and 70 years2. Meet the minimum criteria for APE3. PE short form (PEP) was compatible with acquired premature ejaculation4. International Index of Erectile Function-5 (IIEF-5) is greater than 215. Sign the informed consent form.

#### Exclusion criteria

Although it meets the above diagnostic and inclusion criteria it belongs to:1. Primary premature ejaculation patients2. Merge with other serious systemic diseases or mental or neurological disorders3. Patients without a fixed sexual partner or stable lifestyle4. Spouses who have serious systemic illnesses and cannot cooperate.5. Other conditions deemed unsuitable for participation by the researcher, which may lead to adverse consequences.

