Traditional Chinese medicine (TCM) is regarded as an effective treatment for APE. Unlike Western medicine, TCM requires a holistic approach, tailoring treatment based on the patient’s overall physical condition. In a multicenter survey conducted in China, the intervention rate of TCM for PE reached 39.4% (Sansone et al., 2024). Current literature has demonstrated that the occurrence of APE is linked to psychological disorders, particularly anxiety and depression (Yang et al., 2019). Chaihu-Shugan-San (CHSGS) is a classical prescription to treat depression, Several research teams have confirmed through both clinical studies and animal experiments that CHSGS has a significant effect in alleviating depression and anxiety (Zhu et al., 2022; Zhang et al., 2024; Liu et al., 2020). More studies have focused on the mechanisms by which CHSGS improves depression, and current evidence suggests that the antidepressant properties of CHSGS appear to mediate through multiple interrelated biological systems, including monoaminergic neurotransmission, hypothalamic-pituitary-adrenal axis regulation, brain-derived neurotrophic factor, synaptic remodeling mechanisms, gut-brain axis interactions, and inflammatory pathway modulation. The compound likely exerts its therapeutic effects via multimodal mechanisms involving both direct modulation of these core pathophysiological targets and indirect interactions with downstream molecular effectors, such as receptor systems, intracellular signaling cascades, and epigenetic regulators, with predominant actions localized to central neurochemical processes (Guo et al., 2024). In the clinical practice of TCM andrology, this herbal formula is also commonly used in clinical practice for the treatment of APE. Thus, we hypothesized that CHSGS could alleviate symptoms of APE and enhance patients’ quality of life by improving their emotional state though central nervous system.

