#### Removal criteria

1. Cases in which subjects were found after enrollment not to meet the inclusion criteria2. Use of other medications related to the disease under study3. Those who, after enrollment, were not treated in accordance with the provisions of this study4. Cases in which there was no evaluable record of any post-treatment period.

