### Primary outcome

Drawing on a range of clinical studies, the assessment will be carried out on all patients. Specifically, for patients with APE (Premature Ejaculation), the mean changes from the baseline (the day when the patient commences the protocol) to the end of the observation period (the day when the protocol concludes) will be evaluated in two aspects: the brain MRI and the intravaginal ejaculatory latency time (IELT) measured using a stopwatch, which has been extensively applied and is recommended as a primary outcome measure in clinical trials for APE.

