### Regional homogeneity analysis

SPM12 was used to conduct a regional homogeneity analysis of the resting - state imaging data. First, a paired t - test was used for the comparative analysis of the ReHo images of the APE subjects in each group before and after treatment. Meanwhile, to avoid noise data outside the brain tissue in the results, BrainMask_61 × 73 × 61. img was selected as the whole - brain mask file. The statistical threshold was set at P < 0.005, and the minimum activation cluster was required to be larger than 20 voxels. The results of the regional homogeneity changes in the brain regions before and after treatment were obtained respectively.

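### The entry criteria set no exclusion or drug-free period for current or recent PE treatment, so the within-arm before/after IELT and fMRI changes can carry the effect of earlier treatment

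*Protocol article*

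**What the plan says.** The protocol article gives its entry rules as two numbered lists of five items each. The inclusion list asks for age 18 to 70, acquired PE ("Meet the minimum criteria for APE"), a compatible PEP, an IIEF-5 above 21, and consent. The nearest exclusion is "Merge with other serious systemic diseases or mental or neurological disorders", which names disorders and no drug. The fifth exclusion is discretionary: "Other conditions deemed unsuitable for participation by the researcher, which may lead to adverse consequences". Neither list mentions an SSRI, another PE drug, CHSGS or another herbal product.

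Medication appears only under Removal criteria, item 2: "Use of other medications related to the disease under study". It carries no time window.

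Table 1 places IELT and MRI at enrolment, then allocation, then treatment in weeks 1 to 4, with the second IELT and MRI at week 4. It shows no washout or run-in.

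The Primary outcome section evaluates "the mean changes from the baseline (the day when the patient commences the protocol) to the end of the observation period" for both MRI and stopwatch IELT. For fMRI, the only comparison described is in Regional homogeneity analysis: "a paired t - test was used for the comparative analysis of the ReHo images of the APE subjects in each group before and after treatment". The third aim in the Introduction also correlates brain change with clinical improvement within each group.

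On usual care, the Introduction says that "this herbal formula is also commonly used in clinical practice for the treatment of APE" and that "the intervention rate of TCM for PE reached 39.4" per cent. Recruitment is from the urology clinic of a TCM hospital.

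**The concern.** Read as a site would apply it, a man who takes paroxetine, dapoxetine or CHSGS, or who stopped last week, can be enrolled if he otherwise meets the criteria. His baseline IELT and scan are then taken on or just after that treatment. If he stops it when the capsules start, removal criterion 2 does not catch him. If he continues his own paroxetine or CHSGS, it is unclear whether a study drug counts as another medication.

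His change from baseline then combines loss of the old effect with the effect of the study capsules. A paired before/after test cannot separate the two. Stopping an earlier treatment may also move IELT and ReHo in the same men, which would create a correlation within an arm that has nothing to do with the study drug. Without a record of earlier treatment, no later analysis can identify these men, and a baseline scan cannot be repeated once treatment has begun.

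**Working it through.** **Inputs from the article.** There are 21 men per arm in four arms, and 4 x 21 = 84 reproduces the stated total. The article gives no figure for the share previously treated or for the size of any residual effect, so both are assumed.

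**Assumptions.** A share f of men has a baseline raised by c through earlier treatment. That shift is gone by week 4 and adds to the study-drug effect. Values of f are 10%, 20% and 39.4%. The last is the survey rate for any TCM in PE and serves only as an upper value.

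**Step 1: within-arm change.** An unaffected man in an arm with effect d changes by d. An affected man changes by d - c. The arm mean is (1 - f)d + f(d - c) = d - f*c.

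| f | men of 21 | shift in each arm's mean change |
|---|---|---|
| 10% | 2.1 | -0.10c |
| 20% | 4.2 | -0.20c |
| 39.4% | 8.3 | -0.39c |

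For IELT on the log scale, suppose earlier treatment had multiplied latency by 2, so c = ln 2. At f = 20% the factor on each arm's geometric mean change is exp(-0.20 x ln 2) = 0.871, a 13% fall in the placebo arm with no study drug involved.

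**Step 2: between-arm contrast.** Active minus placebo is (d_active - f*c) - (d_placebo - f*c) = d_active - d_placebo. The expected shift is 0. On the ratio scale the factor 0.871 appears in both arms and cancels.

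**Step 3: chance imbalance.** The difference between two arms of 21 in the share affected has SD sqrt(2f(1 - f)/21). This contributes 0.09c at 10%, 0.12c at 20% and 0.15c at 39.4% to the contrast, with mean 0.

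**Step 4: per-group correlation.** If earlier treatment shifts baseline IELT by c1 and baseline ReHo by c2, the mixture adds f(1 - f)*c1*c2 to the within-arm covariance of the two changes: 0.09, 0.16 and 0.24 times c1*c2. This arises within an arm, so randomisation does not remove it.

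**Step 5: do the existing rules close the gap?**
- Exclusion 2 concerns disorders. The Introduction describes SSRIs as given to delay ejaculation, so a user need have no mental disorder.
- Exclusion 5 depends on the researcher's judgement and is tied to adverse consequences.
- Removal criterion 2 has no look-back and does not reach a man who stopped just before the capsules.
- Removal criterion 1 covers failure of inclusion criteria only.

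**The case against.** The strongest reply is that the trial is randomised with a placebo arm. A reader might infer that the estimated effects against placebo are biased by f*c. Step 2 shows that they are not: the term is common to all arms and cancels in expectation. The article lists independent-samples t-tests and analysis of covariance for clinical data, and its third aim is worded as a comparison with placebo. This part of the objection stands. It does not rescue the paired ReHo test, which is the only fMRI comparison described, or the per-group correlations.

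Second, the entry rules limit exposure. Three senior physicians must agree on acquired PE, with latency usually about 3 minutes or less. A man whose treatment has doubled or tripled his latency is less likely to qualify, so a large f together with a large c is implausible. The 39.4% covers any TCM for PE. It is not CHSGS use, current use, effective use or use in this clinic. This stands, and the upper row of the table is a ceiling. Partial responders and recent stoppers remain eligible.

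Third, a reader might infer that the exclusion and removal lists contradict each other. They do not: silence at entry followed by a removal rule leaves a gap. Continued use of another PE drug is a ground for removal on any reading.

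Fourth, a reader might infer that carry-over to week 4 dilutes the contrasts. The article gives nothing to support or size that, and the model here assumes the old effect has gone.

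Finally, this is a condensed article and the full protocol may hold a medication window. The criteria are printed as numbered lists, which weakens that defence without removing it.

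**Conclusion.** The point holds for within-arm results. As written, the plan lets baseline IELT and scans be taken on or just after earlier PE treatment. This shifts each arm's mean before/after change by -f*c, from -0.10c at f = 10% to at most -0.39c at f = 39.4%, and can create brain-clinical correlations within an arm. The size depends on the assumed f and c, on the old effect being gone by week 4, and on additivity with the study drug.

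The documents do not support the wider claim that change from baseline tells nothing about the study drug. Randomised contrasts with placebo keep an expected shift of 0 unless there is carry-over or earlier treatment alters the response to the study drug. Their cost is added noise and chance imbalance with SD 0.09c to 0.15c. This is a cheap improvement that should be made; it does not invalidate the randomised comparison.

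**What to change.** 1. Add an exclusion for PE treatment (SSRI, other PE drug, CHSGS or other herbal product for PE) within a stated window before the baseline IELT and MRI. The sponsor sets the window and applies it identically to all four arms; no length is proposed here.
2. Record earlier PE treatment at enrolment in the case report form, so that its effect can be examined.
3. Reconcile the removal criteria with the new exclusion. Criterion 2 should cover any non-study PE medication used after baseline, whether continued or newly started, and should say that this includes a man's own paroxetine or CHSGS. Limiting it to medication started after randomisation would miss men who continue an earlier drug. Criterion 1 should cover breaches of exclusion as well as inclusion criteria.

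The cost is one criterion, one form item and two clarified rules, with no added visits or procedures. There will be some screen failures or delayed entries. If earlier treatment is common at this single centre, they may be more than a few, which matters when 84 men are needed.

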#### Removal criteria

1. Cases in which subjects were found after enrollment not to meet the inclusion criteria2. Use of other medications related to the disease under study3. Those who, after enrollment, were not treated in accordance with the provisions of this study4. Cases in which there was no evaluable record of any post-treatment period.

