#### Dropout criteria

1. The occurrence of serious adverse events, complications and special physiological changes, it is not suitable to continue to receive the trial2. The trial process of self-withdrawal3. Due to a variety of reasons caused by the end of the course of treatment, namely, withdrawal from the trial, lost to visit the case4. Incomplete information, affecting the effectiveness and safety of the judgment.The reason for removal should be recorded in all cases of exclusion or detachment. Any adverse reactions during treatment are included in the adverse reaction statistics.

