### Data analysis

#### Clinical variables analysis

Two blinded evaluators will conduct the analysis of clinical data using SPSS 22.0 (SPSS Inc., Chicago, IL). Missing data analysis will be carried out in accordance with the intention - to - treat (ITT) principle, taking into account the baseline characteristics.

The clinical scores of the subjects will be examined through Pearson correlation analysis. All clinical data in this study will be presented in the following ways:1. Continuous measurement data will be presented as the mean ± standard deviation (SD), along with the mean, SD, median, and interquartile range.2. Categorical data will be presented as counts and percentages.

The following analysis tools will be employed: the Cochran - Mantel - Haenszel (CMH) test or nonparametric test, an independent samples t - test, and a two - sided test. Additionally, analysis of covariance, covariance analysis, generalized estimating equations, chi - square (
$x^{2}$
) tests, and linear regression will be applied to all available and appropriate data. A P - value <0.05 will be considered statistically significant.

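### The removal criteria take randomised patients out for reasons arising after treatment starts, which conflicts with the stated intention-to-treat handling of missing data and could bias the arm comparisons

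*Protocol article*

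**What the plan says.** The Removal criteria, under Participants in the Protocol article, give four grounds:

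1. "Cases in which subjects were found after enrollment not to meet the inclusion criteria"
2. "Use of other medications related to the disease under study"
3. "Those who, after enrollment, were not treated in accordance with the provisions of this study"
4. "Cases in which there was no evaluable record of any post-treatment period"

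The Dropout criteria form a separate list. For removed and dropped-out cases alike, that section adds that "The reason for removal should be recorded in all cases of exclusion or detachment" and that adverse reactions stay in the safety statistics. It does not say whether efficacy data from removed patients are kept.

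Under Clinical variables analysis, the article says: "Missing data analysis will be carried out in accordance with the intention - to - treat (ITT) principle". The same section ends its list of methods with "linear regression will be applied to all available and appropriate data", without saying what makes data appropriate.

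Outcome assessment says that data on completers and on patients who discontinue will both be documented. Table 1 schedules IELT, PEP, CIPE, the TCM score and MRI at enrolment and at week 4 only.

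**The concern.** Criteria 2, 3 and 4 describe things that happen after treatment starts, so they act on randomised patients. Each can be a consequence of the allocated treatment. Side effects may lead a patient to stop, lack of effect may lead him to take something else, and either may lead him to miss the final visit. Removing such patients gives up the protection of randomisation.

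The aims in the Introduction are comparisons between arms, so the main contrasts are exposed. Uneven removal is possible on the article's own account. Two arms contain paroxetine and two do not, and the Introduction says drugs of this class carry side effects and that many patients comply poorly. A patient without benefit, for instance on placebo, might take other medication and be removed under criterion 2. Blinding does not prevent this, because the treatment itself can trigger the event.

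**Working it through.** **Step 1: the texts side by side.**

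- *Criterion 4 against the ITT sentence.* Whether a patient has any evaluable post-treatment record can be judged only once follow-up is over, so this is a rule about the data set and not about stopping treatment. Since Table 1 schedules outcomes only at enrolment and week 4, a patient who misses week 4 has no scheduled post-treatment outcome and meets criterion 4. He is also the patient whose missing data are to be handled by intention to treat. The conflict is direct.
- *Criteria 2 and 3 against the ITT sentence.* These patients may have complete outcomes, and the sentence speaks only of missing data. The conflict follows by implication: a plan that keeps patients with no outcome because of how they were randomised cannot consistently drop patients with outcomes because they deviated.
- *Criterion 1* concerns eligibility, which treatment does not cause. The bias argument does not rest on it.

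**Step 2: the plan's own figure.** Study design gives 21 per group in four groups: 4 × 21 = 84, which reproduces. It needs 15 per group, so the margin is 21 − 15 = 6, or 6/21 = 28.6%. The article states no loss rate. This figure is back-calculated, and the margin was set for dropout and head movement in the scanner.

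**Step 3: illustration of size.** From the article: 21 per arm and a 0.05 significance level, with a two-sided test and a t-test among the listed methods. Assumed: the number removed per arm, and the correlation ρ between a patient's tendency to be removed and his outcome. Setting: two arms, no true effect, normal outcome in SD units, the patients most prone to removal taken out, 40,000 simulated trials per scenario. Entries are the false mean difference in SD, with type I error in brackets.

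| ρ | 3 vs 0 removed | 6 vs 2 removed | 6 vs 0 removed |
|---|---|---|---|
| 0.3 | 0.07 (5.6%) | 0.08 (5.8%) | 0.14 (6.9%) |
| 0.5 | 0.12 (6.9%) | 0.14 (7.5%) | 0.23 (10.5%) |
| 0.8 | 0.20 (10.7%) | 0.22 (12.9%) | 0.37 (21.1%) |
| 1.0 | 0.25 (14.3%) | 0.28 (20.1%) | 0.46 (31.9%) |

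Reference cases:

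- No one removed: difference about 0, type I error 4.8% to 5.0%.
- 6 versus 0 removed at random: difference about 0, type I error 5.1%.
- 6 versus 6 removed in relation to outcome: no mean bias, type I error 5.1% to 11.0%. The retained values are no longer independent, so the ordinary t-test does not fit them.

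**Step 4: cross-check.** Removing the lowest fraction p of a normal distribution raises the mean by φ(z_p)/(1 − p), multiplied by ρ when the correlation is below 1. At p = 6/21 this is 0.476 SD for ρ = 1 and 0.5 × 0.476 = 0.238 SD for ρ = 0.5. The simulation gives 0.46 and 0.23. The small gap arises because the formula is for a large sample.

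**Scale.** With 21 per arm, the difference detectable with 80% power is (1.960 + 0.842) × √(2/21) = 0.86 SD. The largest false difference in the table is about half of that (0.46/0.86 = 0.53).

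**The case against.** The removal list stands under Participants, not under data analysis, and the article never says in words that removed cases leave the efficacy analysis. Intention to treat is the only analysis principle it names, and it documents data on patients who discontinue. An ITT set and a per-protocol set can coexist, and analysis sets are often defined in a statistical analysis plan, which is not shown here.

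This narrows the point without removing it. Criterion 4 makes sense only as a data-set rule, and removal is listed apart from dropout. Nothing shown limits the list to a secondary set. The finding is that two stated rules cannot both govern the same analysis, not that analysis sets are undefined.

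A reader might infer more than the article supports:

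- *That the whole analysis is declared ITT.* The sentence covers the missing-data analysis.
- *That the Dropout criteria clash as well.* One of them is "Incomplete information, affecting the effectiveness and safety of the judgment", but classing a patient as a dropout does not in itself contradict ITT.
- *That the plan expects to remove 28.6% of patients.* That figure comes from an imaging allowance which includes head movement, and head movement does not affect IELT.
- *That a shift near 0.46 SD is to be expected.* It needs removal in one arm only and perfect correlation with outcome.
- *That removal will be uneven, or that its direction is known.* The Introduction mentions cost alongside side effects in its remarks on these drugs. Here capsules are provided for four weeks, on the same capsule schedule in every arm. Patients removed for side effects need not be the worst responders.

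**Conclusion.** The conflict stands: direct for criterion 4, by implication for criteria 2 and 3. Applying the list to the primary IELT comparison could bias it, on two conditions: removal must be related to outcome, and it must differ between arms. Both are plausible, and neither is established by the article. The direction could vary from one contrast to another.

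The size cannot be derived from the article. The illustrations run from 0.07 SD (3 versus 0 removed, ρ = 0.3) to 0.46 SD (6 versus 0, ρ = 1.0), with type I error from 5.6% to 31.9% against a nominal 5%. They show what uneven selection can do and are not a forecast. The matter should be settled before unblinding, because choosing between the two rules after outcomes are known would amount to choosing the result.

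**What to change.** Reconcile the Removal criteria, the Dropout criteria and the Clinical variables analysis as follows:

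1. State that the removal criteria do not take randomised patients out of the primary IELT comparison, and analyse all 84 in the arm to which they were randomised.
2. Seek week-4 outcomes from patients who stop treatment, deviate or take other medication. The protocol already provides for documenting data on those who discontinue.
3. Handle remaining missing values by a prespecified method using arm and baseline, such as multiple imputation or a baseline-adjusted model, with a sensitivity analysis. Other week-4 scores will help little, since a patient who misses week-4 IELT will usually miss those too.
4. Keep the removal list for a per-protocol sensitivity set, fixed before unblinding.
5. For MRI, allow exclusions for image quality only, judged blind to arm.

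Most of the cost is wording. The real effort is in follow-up, because stopwatch IELT needs partnered intercourse and MRI needs a visit, so a phone call will not replace week 4. The estimated effect may be somewhat diluted by patients who did not take treatment as planned.
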